**Methodology**

1. Patient Recruitment: All trauma patients with a survivable injury and ISS (decision) will be entered into the study. 100 trauma patients with a brain injury and 100 trauma patients without a brain injury will be studied. The study team will liaise with the emergency department at UHB for local trauma.
   1. Patient journey: Demographics will be entered into a patient database, a schedule of sampling will then be generated to allow the patient to be followed through the study.
   2. Insults: initial injury and insults - baseline GCS score, post-traumatic amnesia, surgical intervention, infection, sepsis, ICP, cerebral blood flow and oxygenation, seizure.
   3. Timings: Admission, surgery, ventilation days, ICU days, discharge, rehabilitation, time to recovery.
2. Measurements and sample collection: The following measurements will be made on samples taken from point of injury through to six month follow-up. The schedule appears in table 1.
   - 1. *Venous blood*. Venous access for drugs and fluids is gained early in trauma care at point of injury, however blood would not routinely be withdrawn as there are no useful clinical tests at this stage currently. We propose to withdraw 20mls at this point for analysis of the early biomarker milieu. An additional 20mls of venous blood will be taken at subsequent time-points. These will be analysed for biomarker levels and metabolomics. Genomic analyses will be carried out on mitochondrial and nuclear DNA, including mitochondrial DNA haplogroups, Apoliprotein E haplotypes and genes of the MToR pathway.
   1. *Micro-diasylate*. Micro-dialysis is used in routine clinical practice to monitor cerebral perfusion. The small amount of diasylate generated would normally be discarded in clinical practice, we propose to recover it for analysis. The diasylate will be snap frozen following recovery and sent to DSTL for analysis.
   2. *CSF*. Where CSF is withdrawn in normal clinical practice an additional 5 mls will be withdrawn for biomarker analysis.
   3. *Imaging.* MRI, MRS, DTI, will be performed in accordance with the schedule at table 2.
      1. MRI: T1, T2, FLAIR, DWI, ADC sequences will be acquired on a 1.5T scanner in the UHB inpatient imaging department.
      2. MRS: sequences will be acquired on a 1.5T scanner in the UHB inpatient imaging department.
      3. DTI: sequences will be acquired on a 1.5T scanner in the UHB inpatient imaging department.
   4. *Test Of Memory Malingering (TOMM).* The TOMM is administered by a trained clinical psychologist, it provides a quantification of effort and helps to validate findings of routine clinical questionnaires, it is not transparent to the participant. TOMM score sheet annex l. *Neurological Assessment Battery (NAB)*. A short version is administered which quantifies cognitive sequelae, it is in questionnaire format.
   5. *Trans-cranial Magnetic Stimulation (TMS).* This will be used to explore the neurophysiology behind how the injured brain learns using protocols that are well established and validated in healthy volunteers. Participants will undergo two bouts of single pulse TMS at frequencies no greater than 0.67 Hz before and after a period of learning. The learning task involves seating the participant in front of a computer and tasking them to track a cursor presented on the screen as accurately as possible. For each of the target lines presented, performance will be quantified as root mean square error between the actual and target traces. The change in activation threshold will be measured before and after which provides insight into the underlying changes. This will be performed at 1 year.
   6. *EEG.* The p300 event related potential will be recorded for participants using an auditory oddball paradigm. Latency will be recorded at the scalp electrode with greatest response, EEG itself is as per standard neurophysiological clinical practice. This will be performed at 1 year.
   7. *ERG*. This is recorded using a standard ISCEV protocol for flash and pattern and multifocal stimuli. Participants have three electrodes placed on the forehead and either side of the eyes and a very fine DTL loop electrode placed in the inferior conjunctival fornix which is painless. Recordings of responses to the stimuli are taken following light and dark adaptation. This will be performed at 1 year.
   8. *VEP*. A limited form of EEG is recorded over the occipital cortex to record higher level responses to flash and pattern and multi-focal stimuli, again to the ISCEV standard protocols. This will be performed at 1 year.
   9. *Pupillometry*. This utilises a device to accurately and sensitively assess the pupillary reflexes giving information on the pathways subserved. This will be performed during the first 30 days.
3. Locations:
   1. Sample collection at point of injury will be conducted by West Midlands Ambulance Service.
   2. Routine blood analysis will be performed as per normal clinical practice by UHB haematology and biochemistry laboratories.
   3. Biomarker assays will be performed at DSTL and UoB.
   4. Genomic analyses will be carried out at UoB
   5. MRI Imaging will be performed in the inpatient MRI department, UHB.
   6. Trans-cranial Magnetic Stimulation, EEG and TOMM will be conducted in the outpatients neurophysiology department of UHB.

Table 1. Schedule of sample analysis

| Time | Sample | Measurement |
| --- | --- | --- |
| 0 (point of injury) | 20mls venous blood | Biomarkers analysis |
| Day 1 (UHB ED) (if no point of injury sample taken) | 20mls venous blood | Biomarkers analysis |
| Day 1 (6-12hrs post injury) | 20mls venous blood | Biomarkers analysis |
| Day 3 | 20mls venous blood | Biomarkers analysis |
| Day 1-14 | Micro-diasylate  CSF (if available) | Biomarkers analysis |
| Day 180 (+/-30) | 20mls venous blood | Biomarkers analysis, Genetic analysis |

Table 2. Schedule of Imaging

| Time | Imaging | Notes |
| --- | --- | --- |
| Day 1-30 | MRI or MRS or DTI | Random selection of patients once stable |
| Day 180 (+/-30) | MRI or MRS or DTI | Same modality as before for comparisom |
| Day 360 (+/-30) | MRS | If 180 day MRS scan abnormal |

Table 3. Schedule of Outcome Measures

| Time | Measures | Notes |
| --- | --- | --- |
| Day 1-30 | Pupillometry | Where possible |
| Day 180 (+/-30) | Cognitive/psychological questionnaires |  |
| Day 360 (+/-30) | Cognitive/psychological questionnaires  TMS  ERP |  |

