**Hypotheses**

The hypothesis to be tested is that biomarkers of neurotrauma may give specific prognostic information for an individual patient to inform acute and sub-acute treatment stratification and future prognosis. Measurements of biomarkers taken after trauma will be correlated with outcome measures at 6 and 12 months.

Secondary hypotheses are that novel biomarkers exist and may be identified; genetic factors are important modulators of outcome.

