**Statistical Analysis**

Data will be analysed using SPSS. Descriptive statistics will be determined on parametric and non-parametric data. The independent variables are age, sex, ISS/NISS, type of injury, MTOR activity status. The primary dependent variables include biomarker levels, imaging analysis, TMS threshold and cognitive/psychological scoring. Exploratory assessment of data will be completed using analysis of co-variance and ordinal analysis of outcome. The spread of the means will be given as standard error of the mean. Differences in the means are considered significant if p<0.05. Psychological and cognitive scoring will undergo correlation analysis using Spearman’s rank correlation coefficient. They will also be subject to Rasch analysis. Multivariate regression analysis will be used to identify factors with significant impact on outcome.

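### Genetic analysis is scheduled only on the Day 180 blood sample, so patients who die earlier have no scheduled genotype and the genetic hypothesis can be tested against 6-month Glasgow Outcome Score only in survivors who attend

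*Protocol*

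**What the plan says.** The Hypotheses section names, as a secondary hypothesis, that "genetic factors are important modulators of outcome". The Outcome Measures section makes Glasgow Outcome Score at 6 months the primary outcome.

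The Methodology section, under venous blood, sets out the laboratory work: "Genomic analyses will be carried out on mitochondrial and nuclear DNA, including mitochondrial DNA haplogroups, Apoliprotein E haplotypes and genes of the MToR pathway". It gives no sampling time for this. For timing, the same item refers the reader elsewhere: "The schedule appears in table 1".

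Table 1 has four acute blood rows: point of injury, emergency department (if no point-of-injury sample was taken), 6 to 12 hours, and Day 3. All four are for biomarkers only. Two of them read "Day 1 (6-12hrs post injury) | 20mls venous blood | Biomarkers analysis" and "Day 3 | 20mls venous blood | Biomarkers analysis". Only the Day 180 (+/-30) row reads "Biomarkers analysis, Genetic analysis".

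The Sampling - Blood text also says that genetic analysis will be done. Its word 'initially' describes which factors are examined first, not when blood is taken. Nothing in the protocol provides for DNA from earlier or stored blood, or for patients who die before the Day 180 visit.

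**The concern.** The exposure (genotype) is measured at about the time the outcome falls due, and only in people alive and present to give blood. Death is ordinarily the lowest category of the Glasgow Outcome Score. The protocol does not list the categories, so I take that as given. Patients in that category have a known outcome and no scheduled genotype, which is selection on the outcome itself.

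A variant that worsens outcome across the whole scale would appear weaker than it is. A variant that acts only through early death would show no association at all. An analysis plan cannot repair this later, because it cannot supply a genotype for which no DNA was set aside.

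**Working it through.** **No stated figure to reproduce.** The protocol gives no power calculation for the genetic hypothesis. Its one sample size (10 per group, Fisher's exact test, 80% against 10%) concerns biomarker response and does not bear on this point.

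**Step 1: the direction, in closed form.** Suppose a variant doubles death before the visit from 10% to 20% and leaves poor outcome among survivors at 30%. These rates are assumed.
- Death or poor outcome, non-carriers: 0.10 + 0.90 × 0.30 = 0.37.
- Death or poor outcome, carriers: 0.20 + 0.80 × 0.30 = 0.44.
- Odds ratio in all patients: (0.44/0.56) / (0.37/0.63) = 1.34.
- Odds ratio in survivors: (0.30/0.70) / (0.30/0.70) = 1.00.

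The association disappears among survivors.

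**Step 2: the effect on power, by simulation.** The 100 brain-injured patients are from the protocol; everything else is assumed:
- 25% carriers.
- Non-carrier probabilities on a five-category score of d (death), 0.02, 0.13, 0.20, and the remainder for good recovery.
- Carriers shifted by a common (proportional) odds ratio of 3 towards worse outcome.
- Two-sided Wilcoxon test at 0.05.

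The mortality d is the non-carrier rate. Carrier mortality is 3d/(1 − d + 3d). Overall mortality is 0.75 × non-carrier + 0.25 × carrier. For d = 10%, carrier mortality is 0.30/1.20 = 25%, so overall mortality is 0.75 × 10% + 0.25 × 25% = 13.75%.

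| Non-carrier mortality | Overall mortality | Power, all patients | Power, survivors only |
|---|---|---|---|
| 2% | about 3% | about 72% | about 66% |
| 5% | about 7% | about 72% | about 58% |
| 10% | about 14% | about 72% | about 46% |
| 20% | about 26% | about 72% | about 28% |
| 30% | about 37% | about 72% | about 18% |

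Full-data power varies only between about 71% and 74% across these rows.

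**Step 3: sensitivity.**
- With a common odds ratio of 2, power with all patients is about 38%. In survivors it is about 28% at 5% non-carrier mortality and about 18% at 20%.
- If the variant acts on death alone (odds ratio 4, non-carrier mortality 20%), carrier mortality is 0.80/1.60 = 50% and overall mortality 0.75 × 20% + 0.25 × 50% = 27.5%. Power falls from about 63% to about 5%, the false-positive rate of the test.

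**The case against.** Several objections stand in whole or in part.

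- **The hypothesis is secondary.** The main biomarker question uses the acute samples and is untouched, so a reader should not infer that the study's primary aim is compromised.
- **Deaths may be few.** Entry requires a survivable injury, and no mortality rate is given. At 2% non-carrier mortality the loss is small. Early sampling would also not give an adequately powered test of a modest effect: with an odds ratio of 2, full-data power is only about 38%.
- **Waiting has some value.** Acute samples may be taken under the emergency provision, followed by consultee advice and then the patient's own consent once capacity returns. By Day 180, personal consent to genotyping is more likely. The protocol does not give this as its reason, and the consent forms are not shown.
- **The unseen annexes may cover aliquots.** The team instructions and blood-sampling guidelines are listed but not shown. This lowers certainty, but the Methodology text sends the reader to Table 1, which assigns genetics to one row.

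Three stronger readings are tempting, but the documents do not support them.

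- **Loss to follow-up.** A reader might infer that it does the same damage as death. Most patients lost before Day 180 would have no 6-month score either, so an early genotype would add nothing. It matters only where the score is obtained without a visit. Outcomes measured only in attending survivors, such as the cognitive and neurophysiological measures, are little affected.
- **The regression model.** A reader might infer that every death drops out of it, because "The independent variables are age, sex, ISS/NISS, type of injury, MTOR activity status". But activity status is not said to be a genotype, and no complete-case rule is stated.
- **Every death before 6 months.** The visit window opens at Day 150, so the exact condition is death before the patient's own Day 180 (+/-30) visit.

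**Conclusion.** The point holds for deaths and the Glasgow Outcome Score. As Table 1 stands, the genetic hypothesis can be tested against the 6-month score only in survivors who attend, and an effect acting through early death would be attenuated or missed.

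The size cannot be read from the protocol. Under the assumptions above it runs from minor (about 72% to 66% power at 2% non-carrier mortality) to severe (about 72% to 18% at 30%). It also depends on the assumed carrier rate, odds ratio and outcome distribution; of these, only the odds ratio was varied.

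This should be fixed, but it does not threaten the study's main result. The reasons to act early are that the change is cheap and that a genotype not provided for before death cannot be planned for afterwards.

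**What to change.** 1. In Table 1, assign DNA storage and genetic analysis to an aliquot of the earliest acute blood sample already drawn, with later samples, including Day 180, as back-up.
2. Release the aliquot for genotyping only under the consultee-advice and consent route described in Study Design and Ethical Considerations. Obtain ethics approval that this route covers genetic use.
3. State that the analysis of genotype against Glasgow Outcome Score includes deaths.
4. If early genotyping is not approved, keep the Day 180 sample and state that the genetic conclusions apply only to 6-month survivors who attend.

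The cost is schedule and ethics wording and storage of one aliquot per patient, with no additional blood draw. The real drawback is that genetic use would rest on consultee advice for patients who never regain capacity.

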**Statistical Analysis**

Data will be analysed using SPSS. Descriptive statistics will be determined on parametric and non-parametric data. The independent variables are age, sex, ISS/NISS, type of injury, MTOR activity status. The primary dependent variables include biomarker levels, imaging analysis, TMS threshold and cognitive/psychological scoring. Exploratory assessment of data will be completed using analysis of co-variance and ordinal analysis of outcome. The spread of the means will be given as standard error of the mean. Differences in the means are considered significant if p<0.05. Psychological and cognitive scoring will undergo correlation analysis using Spearman’s rank correlation coefficient. They will also be subject to Rasch analysis. Multivariate regression analysis will be used to identify factors with significant impact on outcome.

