**Outcome Measures**

Outcome of brain trauma will be assessed with cognitive and psychological symptom scoring, TMS threshold measurement and ERP. Initial severity scoring will be assessed with ISS/NISS. Changes in biomarkers will be measured in relation to brain trauma versus non-brain trauma and related to the above outcome assessment.

The primary outcome will be functional status as measured by the Glasgow Outcome Score at 6 months. Secondary outcome measures are functional status as assessed by the Glasgow Outcome Score at 12 months; cognitive and psychological symptom scoring with Post­concussion Symptom Questionnaire­19 (PCSQ­19), Impact of Events Scale – revised (IES­r), Depression and Anxiety Symptom Scale – 21 (DASS­21), PTSD checklist (PCL), Patient Health Questionnaire (PHQ), neurological assessment battery NAB-SM.

Other seconday outcome measures are neurophysiology measures of TMS threshold and Event related potentials.

Developing a better understanding of the relationships surrounding severe brain trauma and biomarkers in development will lead to better clinical understanding, categorisation, prognostication and treatments, both in targeting existing interventions and through development of new treatment in future interventional studies.

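### The declared primary outcome, the Glasgow Outcome Score at 6 months, is missing from the outcome schedule and from the named primary dependent variables, and biomarkers are missing from the listed predictors

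*Protocol*

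**What the plan says.** The Outcome Measures section that follows Statistical Analysis sets the endpoint: "The primary outcome will be functional status as measured by the Glasgow Outcome Score at 6 months". It continues: "Secondary outcome measures are functional status as assessed by the Glasgow Outcome Score at 12 months". Cognitive and psychological symptom scoring, TMS threshold and event-related potentials are also secondary there.

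The Statistical Analysis section uses a different list: "The primary dependent variables include biomarker levels, imaging analysis, TMS threshold and cognitive/psychological scoring". Its independent variables are age, sex, ISS/NISS, type of injury and MTOR activity status. Two sentences there speak of outcome without naming a measure: "Exploratory assessment of data will be completed using analysis of co-variance and ordinal analysis of outcome" and "Multivariate regression analysis will be used to identify factors with significant impact on outcome".

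In Methodology, under "Table 3. Schedule of Outcome Measures", the 6-month row reads "Day 180 (+/-30) | Cognitive/psychological questionnaires". The Day 360 row holds questionnaires, TMS and ERP. The Hypotheses section states the main purpose: "Measurements of biomarkers taken after trauma will be correlated with outcome measures at 6 and 12 months".

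**The concern.** A primary outcome should appear in three places that agree: its definition, the visit schedule and the analysis section. Here it appears only in the definition.

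Two things are at stake. The first is collection. Site staff work from the schedule, and a 6-month rating that is not on it may be done unevenly or not at all. The second is pre-specification. The word primary is attached to one endpoint in one section and to four families of variables in another. That weakens the protection against stressing whichever result turns out best.

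The variable roles add to this. The hypothesis is prognostic, so biomarkers must be predictors and outcome the response. The stated roles list biomarkers only on the response side.

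**Working it through.** No effect size or power figure bears on this point, so the check sets the sections side by side.

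| Place in the protocol | Outcomes or variables listed | GOS named? |
|---|---|---|
| Outcome Measures (standalone section), second paragraph | GOS at 6 months primary, at 12 months secondary; questionnaires, TMS and ERP secondary | Yes |
| Same section, first paragraph | Symptom scoring, TMS threshold, ERP | No |
| Study Design, opening paragraph | TMS threshold, ERP, ERG, VEP, questionnaires | No |
| Study Design, outcome subsection | Questionnaires, TMS thresholds, p300, VEP, ERG | No |
| Methodology, itemised measurements | TOMM, NAB, TMS, EEG, ERG, VEP, pupillometry (with samples and imaging) | No |
| Table 3, Day 180 | Questionnaires | No |
| Table 3, Day 360 | Questionnaires, TMS, ERP | No |
| Statistical Analysis, primary dependent variables | Biomarkers, imaging, TMS threshold, cognitive/psychological scoring | No |

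**Schedule.** Two GOS assessments are declared and Table 3 contains 0 of 2. The generic questionnaire entry does not naturally cover the score: Outcome Measures separates functional status, measured by the GOS, from cognitive and psychological symptom scoring, and lists the instruments for the latter. The 6-month window is Day 180 ± 30, that is 180 − 30 = Day 150 to 180 + 30 = Day 210. A rating missed by Day 210 cannot be made later within the window. Planned recruitment is up to 100 per group, so up to 100 + 100 = 200 patients.

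**Meaning of primary.** Of the four families named in Statistical Analysis, two (TMS threshold and cognitive/psychological scoring) are secondary in Outcome Measures. Reading the list as open could admit the GOS as a fifth member (4 + 1 = 5). It would then be one of at least five primary variables, not the single primary outcome, and the conflict over the other two would remain. Nor can all the named variables stand in for a 6-month endpoint: Methodology places TMS at 1 year only, and Table 2 gives a scanned patient one of three imaging modalities.

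**Analysis.** Two sentences could cover the GOS. The ordinal analysis is labelled exploratory, and the regression names no endpoint. The first paragraph of Outcome Measures says biomarker changes will be related to the outcome assessment described above it. What stands above is symptom scoring, TMS and ERP; the GOS comes only in the next paragraph.

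**Variable roles.** Biomarkers are 0 of the 5 listed independent variables and are listed as dependent. That role is correct for one planned comparison, brain trauma versus non-brain trauma, which is also the basis of the sample size in Study Design (80% versus 10% biomarker-positive). It is the wrong role for the prognostic hypothesis.

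**The plan's own figure.** The 10 per group for that comparison reproduces: Fisher's exact test at n = 10 has power 0.937 one-sided and 0.841 two-sided (sidedness is not stated; 11 per group gives 0.905 two-sided). It concerns biomarker positivity, so it neither supports nor undermines the GOS endpoint.

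**The case against.** A reader might infer that the plan neither schedules nor analyses its primary outcome. The protocol does not support that. Outcome Measures fixes the GOS at 6 and 12 months, and visits exist at Day 180 and Day 360. Table 3 is also not exhaustive: it omits ERG and VEP, which Methodology sets at 1 year, so absence from the table does not prove that a measure is unscheduled. The ordinal analysis and the regression on outcome are generic and could take in the GOS. The dependent-variable list is worded as open, and further detail may sit in a statistical analysis plan that is not shown. All of this stands.

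A reader might also infer that biomarkers should not be dependent variables at all, or that the analysis section tests only whether age, sex and ISS predict biomarkers. Neither follows. The comparison with controls needs biomarkers as the response, and the regression sentence and the hypothesis both point to prediction of outcome.

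It is fair to add that only one section uses the term primary outcome, and that it gives one measure at one time. This limits how freely a headline result could be chosen.

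These points do not remove the contradiction. An open list cannot make TMS threshold and cognitive/psychological scoring both primary and secondary. On the most favourable reading, the declared primary outcome has only an exploratory ordinal analysis and a regression that does not name it. A later analysis plan could supply models, but the conflict is between statements already made in the protocol.

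**Conclusion.** The inconsistency is real and wrong as written. Its size is a matter of text: 0 of 2 declared GOS assessments in the outcome schedule, no analysis tied to the score by name, two of four named primary dependent variables classed as secondary elsewhere, and biomarkers absent from the five listed predictors. No bias, loss of power or inflation of error can be calculated, because the protocol gives no GOS distribution or effect size.

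The conclusion assumes that the questionnaire entries in Table 3 are not meant to include the GOS, as the Outcome Measures section implies. If the sponsor did intend that, the scheduling part becomes a matter of clarification, while the conflict over what is primary and the omission of biomarkers as predictors remain. Because the point touches the primary endpoint and costs little to correct, it should be corrected.

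**What to change.** 1. Add the GOS to the Day 180 and Day 360 rows of Table 3 and to the itemised measurements in Methodology, and add it to the outcome list in Study Design.
2. In Statistical Analysis, name the GOS at 6 months as the single primary outcome for the prognostic hypothesis, and make its ordinal analysis the primary rather than an exploratory analysis.
3. Label TMS threshold and questionnaire scores secondary there, in line with Outcome Measures.
4. Add biomarker levels to the predictors for that analysis. Keep them as dependent variables in the brain-trauma versus control comparison, and say which role applies to which analysis.

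The choice of ordinal model and any transformation of the biomarkers can be left to the statistical analysis plan. The cost is a wording amendment, plus making sure that the rating is done at two follow-up visits already planned. No new visit is needed and the recruitment target does not change. The amendment should be settled before outcome data are examined.

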**Study Design**

This is a cohort study to categorise the traumatic brain injury population at UHB. Brain biomarkers, serum, micro-diasylate, CSF and imaging will be measured in two groups of patients. Outcome will be assessed by TMS threshold, ERP, ERG, VEP and cognitive and psychological questionnaires will be performed. The two groups of patients will be:

The study group - patients who have suffered a head injury presenting or transferred to UHB.

The control group - patients admitted with non-head trauma matched to the study group by ISS severity and demographic.

Patients for inclusion will be identified at point of injury or as soon as possible after presentation to UHB upto 1 hour post injury. For samples taken pre-hospital where patients are unable to consent these will be taken, subject to a favourable REC opinion under the Mental Capacity Act ‘waiver’ for research in emergency situations. Advice will be sought from a consultee as soon as practicable following presentation to hospital and consent will be sought from the patient once capacity has been regained. Information in the form of the included Patient Information Sheets or Consultee Information Sheet will be provided; consent or advice will be recorded on the appropriate written forms annexes c-i.

*Inclusion criteria:*

Study group - Patients who have sustained a head injury resulting in presentation to UHB within 1 hour of injury.

Control group - non-head trauma patients matched to control by severity (ISS) and demographic.

*Exclusion criteria:*

Children under the age of 18 years. For the control group those with a recent head injury or known neurological condition.

Our conservative assumption is that 80% of head injured patients will show a positive biomarker response with 10% of non-head injured patients showing a positive response. Using fishers Exact test (power0.9; alpha 0.05; 1:1 control subject ratio) would predict 10 patients in each group. However head injuries and trauma in general demonstrates much heterogeneity and to allow comparison across modalities and sub-groups we intend to recruit up-to 100 patients to the study group and the control group.

*Sampling - Blood*

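### The Statistical Analysis and Outcome Measures sections contradict each other on what is primary: one names only the 6-month Glasgow Outcome Score, the other omits it and lists measures called secondary elsewhere

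*Protocol*

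**What the plan says.** Two consecutive sections of the protocol assign primary status.

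- **Statistical Analysis:** "The primary dependent variables include biomarker levels, imaging analysis, TMS threshold and cognitive/psychological scoring". The GOS does not appear anywhere in this section. On methods it says "Exploratory assessment of data will be completed using analysis of co-variance and ordinal analysis of outcome", then "Differences in the means are considered significant if p<0.05". Spearman correlation and Rasch analysis are assigned to the psychological and cognitive scores. The section closes with "Multivariate regression analysis will be used to identify factors with significant impact on outcome", without saying which outcome. Its independent variables are age, sex, injury severity, injury type and MTOR status; biomarkers are not among them.
- **Outcome Measures (the section after Statistical Analysis):** "The primary outcome will be functional status as measured by the Glasgow Outcome Score at 6 months". It continues "Secondary outcome measures are functional status as assessed by the Glasgow Outcome Score at 12 months; cognitive and psychological symptom scoring", followed by the named questionnaires, and then "Other seconday outcome measures are neurophysiology measures of TMS threshold and Event related potentials".

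The sample-size paragraph in Study Design rests on a further quantity, a binary biomarker response: "80% of head injured patients will show a positive biomarker response with 10% of non-head injured patients", compared with Fisher's exact test.

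**The concern.** A reader of Outcome Measures would expect one primary analysis, of the GOS at 6 months. A reader of Statistical Analysis would expect primary results on biomarkers, imaging, TMS and questionnaires, and would not know that the GOS was collected. TMS threshold and the questionnaire scores have opposite status in the two sections.

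What is at stake is the reading of the results. If the GOS shows nothing, its ordinal analysis can be described as exploratory while a positive TMS or questionnaire finding is presented as primary with support from the protocol. If the GOS is positive and the rest is not, the other section can be cited. The label on the headline result would depend on which section is cited once the data are known.

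**Working it through.** **1. The plan's own figure.** Inputs from Study Design: response 0.80 versus 0.10, Fisher's exact test, power 0.9, alpha 0.05 (sidedness not given), 1:1 allocation, stated answer 10 per group. Power is the sum, over all pairs of counts that Fisher's test rejects, of the product of the two binomial probabilities.

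| n per group | Power, two-sided | Power, one-sided |
|---|---|---|
| 9 | 0.830 | 0.888 |
| 10 | 0.841 | 0.937 |
| 11 | 0.905 | 0.965 |

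The smallest n reaching 0.9 is 10 one-sided and 11 two-sided, so the stated 10 is reproduced or missed by one. The calculation is not the problem. It sizes biomarker positivity between head-injured and control patients, so it does not settle whether the GOS or the list in Statistical Analysis is primary.

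**2. The two sections side by side.**

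| Variable | Statistical Analysis | Outcome Measures |
|---|---|---|
| GOS, 6 months | not named | the primary outcome |
| GOS, 12 months | not named | secondary |
| Cognitive and psychological scores | primary dependent | secondary |
| TMS threshold | primary dependent | secondary |
| Event-related potentials | not named | secondary |
| Biomarker levels | primary dependent | compared between groups and related to outcome; not ranked |
| Imaging | primary dependent | not listed |

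Two of the four items called primary are secondary in the other section, and the other two are not ranked as outcomes there. The only primary outcome in Outcome Measures is absent from Statistical Analysis.

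**3. Methods tied to the GOS.** Ordinal analysis is the listed method best suited to an ordered outcome scale, and it sits in the exploratory sentence. (The protocol does not describe the scale; I assume only that it is ordered.) The p<0.05 rule concerns means. Spearman and Rasch are for the questionnaires. The closing regression may cover the GOS but does not say so. The Hypotheses section makes biomarkers the source of prognostic information, yet Statistical Analysis lists them as dependent and not as independent variables.

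**4. Where else the GOS is missing.** It is absent from the outcome list in Study Design, from the outcome description under that section, from Table 3 at Day 180 and Day 360, and from the opening sentence of Outcome Measures.

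**5. Scale, for illustration.** Assume one true-null test at 0.05 in each of the four families and that any one success counts.

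- Independent tests: 1 − 0.95^4 = 1 − 0.8145 = 0.185.
- With the GOS as a fifth: 1 − 0.95^5 = 1 − 0.7738 = 0.226.
- If the biomarker family is not null, as the planning rates imply, three remain: 1 − 0.95^3 = 0.143.
- Any dependence among the four: between 0.05 (complete overlap) and 4 × 0.05 = 0.20 (no overlap).

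**The case against.** The strongest reply is that Outcome Measures already fixes one primary outcome and time point without ambiguity. The list in Statistical Analysis is introduced by *include*, so the GOS may be an unstated further item. The detailed primary test is also commonly left to a statistical analysis plan, which is not at hand. Part of this stands: a missing test specification is not in itself a finding. But an open list could only admit the GOS. It cannot explain why TMS threshold and the questionnaires are primary in one section and secondary in the next. A later plan would have to depart from one of the two.

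A reader might infer more than the documents support, in four ways.

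- *That the study has no single primary test at all.* Only the protocol is available. What can be said is that none in it is explicitly tied to the GOS as primary.
- *That secondary outcomes receive a confirmatory analysis and the primary one does not.* Statistical Analysis calls nothing confirmatory. Its closing regression is not labelled exploratory and could cover the GOS, and Hypotheses plans to correlate biomarkers with outcomes at 6 and 12 months.
- *That TMS at 1 year is a second, separate conflict.* Statistical Analysis gives its variables no time point. The timing clashes only once the 6-month GOS is taken as primary, so it is the same contradiction.
- *That 18.5% is the study's error rate, or a lower bound on it.* The protocol states no rule that any one success suffices. Outcomes are measured in the same patients, so positive dependence could lower the figure, while several measures per family could raise it.

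**Conclusion.** The contradiction stands and rests on the text alone. The protocol gives two incompatible accounts of what is primary, and it does not explicitly tie any analysis to the GOS as primary. Reconciliation is needed before results are seen, because a choice made afterwards would not be credible.

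The size cannot be stated as one number. The 18.5% assumes four independent true-null tests, one per family, and an any-one-succeeds rule; it shows only that the ambiguity is not trivial. The sample-size figure is not in dispute.

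**What to change.** In Statistical Analysis:

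1. Name the GOS at 6 months as the primary dependent variable, with the biomarkers as predictors. Make an ordinal analysis, for example proportional-odds regression, its primary and not exploratory analysis. Proportional odds is one reasonable choice, not the only one.
2. Label the 12-month GOS, TMS threshold, event-related potentials and questionnaire scores secondary, as Outcome Measures does.
3. State separately the role of the head-injury versus control biomarker comparison. It is the only comparison with a sample-size calculation and should not become exploratory by default.

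Elsewhere, add the GOS to Table 3 at Day 180 and Day 360 and to the opening sentence of Outcome Measures.

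These changes settle the primary variable. Which biomarker and sampling time form the primary predictor also needs stating, here or in the statistical analysis plan; otherwise several biomarker tests would share primary status.

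The cost is a few sentences in two sections and entries in one table, with no added patients. The small downside is that TMS or questionnaire results can no longer be claimed as primary.
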